	**SECONDARY**
	- Rate of antenatal corticosteroid use
	- Maternal infection from birth up to 7 and 42 days postpartum
	- Perinatal mortality rate (stillbirths ≥ 20 weeks GA or ≥ 500 g + neonatal deaths before 7 days)
	- Early neonatal mortality rate at 7 days after birth
	- Mean neonatal weight at 7 and 28 days
	- Neonatal and perinatal mortality rates by country
	- Neonatal and perinatal mortality rates by type of setting (health facility based deliveries vs. community based deliveries)
	- Infant mortality rate at 42 days after birth*.*
**Outcome measures in all infants and their mothers**	- Early neonatal mortality (7 days after birth)
	- Neonatal mortality at 28 days after birth
	- Maternal infection from birth up to 7 days postpartum
	- Maternal infection from birth up to 42 days postpartum
	- Infant mortality rate at 42 days after birth
**Process measures**	- Number of women receiving corticosteroids and number of doses
	- Number of referrals
	- Number of health providers trained
	- Number of kits distributed
	- Health providers’ opinions about the kits
	- Number of kits fully used (all doses administered) at site
	- Number of kits partially used (1–3 doses of dexamethasone) at site

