GN sites have different mean birth weights; those from Asian sites are much lower than those from African and Latin American sites. Using the same birth weight (e.g., < 2500 g) as a cutoff point at all sites would include a higher proportion of Asian babies, whose mean birth weights are ~2700 g, and most of them would be SGA babies rather than preterm. To avoid this, we will use different cutoff points for each country to select the 10% smallest babies in each GN site. Using data from the MNH study for each GN site, we set a birth weight cutoff point, rounded to 100 g, that would select the smallest 10% of infants as a proxy for preterm births (< 36 weeks GA). Using this rule, the cutoff point for sites in Argentina, Zambia, and Kenya was 2500 g; for sites in Guatemala and Karnataka, India, was 2400 g; and for sites in Nagpur, India, and Pakistan was 2200 g. The overall prevalence of LBW for all sites according to those weight limits is 8.2%, with an 11.4% neonatal mortality at 7 days. A birth weight of 750 g will be used as a cutoff point for the lower birth weight limit for analysis purposes, except for those GN sites where babies with birth weights < 1000 g are considered abortions.

The primary and secondary outcomes in LBW babies, the outcomes in all infants and their mothers, and the process outcomes (to be measured only in the intervention clusters) are shown in Table
1. LBW babies are defined as newborns with birthweight below the 10^th^ percentile of the site.

**Table 1 T1:** Study outcomes

**Outcome measures in infants with birth weight below 10**^**th**^**percentile and their mothers**	**PRIMARY**
	- Neonatal mortality at 28 days

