#### *Other secondary outcome measures*

The trial will also examine a number of additional clinical and process measures as secondary outcomes. For each of these outcome measures, descriptive statistics will be computed as described in the introductory paragraphs above. Model-based analyses will then be used to examine the effects of the intervention on each of clinical and process measures. For the clinical measures, GEE models will be used to evaluate the effect of the intervention on marginal risk of the outcome, with results reported for both unadjusted analyses and analyses controlling for covariates that differ across clusters. Also, generalized linear mixed models will be used to examine the effect of the intervention on subject-level risks. Again, results will be reported for both unadjusted and adjusted models.

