### Sample size

#### *Effect size*

We expect to increase corticosteroids use from less than 10% to at least 50% among preterm births. From the estimates in the systematic review on the effect of corticosteroids on mortality
[4], we expect an associated relative rate reduction in neonatal mortality of 25%–30%. The estimated effect size is lower than the effect observed in the systematic review of clinical trials
[4], to take into consideration that we will use birth weight as a proxy for GA and therefore will include a proportion of term small for GA babies who may not benefit from receiving corticosteroids.

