#### *Power estimates*

This trial will be conducted using all of the clusters from the MNH registry determined to have the local infrastructure to implement the protocol. On the basis of preliminary information from the site investigators, we anticipate between 90 and 100 clusters with at least 250 annual deliveries (average of 400) to be available for the trial. Assuming that between 8% and 9% of deliveries are premature, we anticipate a mean cluster size of between 50 and 75 premature newborns for an 18- to 24-month trial. For 28-day neonatal mortality, a study size of 90 clusters with at least 60 LBW deliveries per cluster will have a power of slightly more than 80% (Type I error rate of 0.05) to detect a decrease of 30% in neonatal mortality from 13% to 9%. For the outcome of antenatal corticosteroid use among LBW infants, a sample size of 90 clusters with 50 events per cluster has a power of greater than 0.99 to see an increase in utilization from a start-rate of 10%–20% or more.

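### Mean weight at 7 and 28 days exists only for infants alive at that age, so the arm comparison is not protected by randomisation when mortality is expected to differ

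*Protocol article*

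**What the plan says.** Table 1 of the protocol article places "Mean neonatal weight at 7 and 28 days" among the secondary outcomes for infants in the lowest birth-weight group and their mothers. The Outcome measures section defines that group: "LBW babies are defined as newborns with birthweight below the 10^th^ percentile of the site". It adds a floor: "A birth weight of 750 g will be used as a cutoff point for the lower birth weight limit for analysis purposes", with a higher floor at some sites. The upper cutoffs run from 2200 to 2500 g by site.

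The primary outcome in the same infants is death by 28 days. Under Effect size the article states "we expect an associated relative rate reduction in neonatal mortality of 25%–30" (per cent). Under Power estimates the design is "a study size of 90 clusters with at least 60 LBW deliveries per cluster", with slightly more than 80% power "to detect a decrease of 30% in neonatal mortality from 13% to 9" (per cent).

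Under Other secondary outcome measures, the clinical measures are to be analysed by GEE and by generalized linear mixed models. For the GEE models the text specifies "results reported for both unadjusted analyses and analyses controlling for covariates that differ across clusters". That section is worded for risks and does not mention weight or infants who die before they are weighed.

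**The concern.** Weight at day 7 or day 28 can be observed only if the infant is alive. Survival is what the intervention is meant to change. If it works, the intervention arm contributes weights from infants who would have died under control care, and the control arm has no counterpart to them. The two weighed groups are then selected differently, and randomisation no longer makes them comparable.

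The article applies this reasoning elsewhere. In Outcome measures it declines to define the population by gestational age, because the classifying variable should be unrelated to the intervention. Being alive at day 28 is related to the intervention by design.

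The stake is the reading of safety, which is the stated secondary objective. Weight is the only infant outcome in Table 1 that is not a mortality measure. A lower intervention mean could be taken for harm when it reflects added survivors. Conversely, if the intervention raised deaths among the smallest infants, the survivor mean would rise and could mask that harm.

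**Working it through.** **Inputs from the article**
- 28-day mortality of 13% (control) and 9% (intervention), so survival S0 = 0.87 and S1 = 0.91.
- Baseline 7-day mortality in low-birth-weight infants: "with an 11.4% neonatal mortality at 7 days".
- 90 clusters of 60 infants, allocated 1:1, which is 45 clusters and 2,700 infants per arm.
- ICC between 0.01 and 0.05.

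**Assumptions not in the article**
- Two-sided 5% test.
- Weight SD of 300 to 500 g.
- The article's ICC range applies to weight.
- Every survivor is weighed.
- Every infant who would survive under control care also survives under the intervention.
- Weight gap D of 200 to 600 g, where D is how much lighter the additional survivors are than the other survivors.

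**The plan's own figure.** Effective size per arm is 2,700 / (1 + 59 × ICC). At ICC 0.03 (the midpoint, assumed) this is 2,700 / 2.77 = 975, and power for 13% versus 9% is 0.806. That matches the stated figure. ICC 0.01 gives 0.962 and ICC 0.05 gives 0.657. The mortality scenario is therefore a fair basis for what follows; the power itself is not in dispute.

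**Share of additional survivors** = (S1 - S0) / S1
- Day 28, 13% to 9%: 0.04 / 0.91 = 4.4%.
- Day 28, a 25% fall to 9.75%: 0.0325 / 0.9025 = 3.6%.
- Day 7, 11.4% cut by 30% (assumed) to 8.0%: 0.0342 / 0.9202 = 3.7%.

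**Shift in the intervention mean with no true effect on weight** = -share × D. At day 28, with 13% versus 9%:
- D = 200 g: -8.8 g
- D = 400 g: -17.6 g
- D = 600 g: -26.4 g

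**Standard error of the arm difference.** Survivors per cluster average 60 × 0.89 = 53.4, so 45 × 53.4 = 2,403 per arm. Effective n = 2,403 / (1 + 52.4 × ICC), and SE = SD × sqrt(2 / effective n).
- SD 300 g, ICC 0.01: effective n 1,577, SE 10.7 g.
- SD 400 g, ICC 0.03: effective n 934, SE 18.5 g.
- SD 500 g, ICC 0.05: effective n 664, SE 27.4 g.

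**Chance of a nominally significant lower weight in the intervention arm** = P(Z > 1.96 - |shift| / SE), which is 2.5% when there is no shift.
- Smallest shift, largest SE: 8.8 / 27.4 = 0.32, about 5%.
- Middle case: 17.6 / 18.5 = 0.95, about 16%.
- Largest shift, smallest SE: 26.4 / 10.7 = 2.47, about 69%.

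**Dependence on which infants are saved.** Birth weights were simulated between 750 and 2400 g with mortality falling as weight rises (weight distributions and mortality slopes assumed) and mortality moving from 13% to 9%. The shifts, expressed in birth weight, were:
- mortality reduced proportionally at all weights: -2 to -25 g;
- all saved infants under 1800 g: -25 to -32 g;
- all saved infants 1800 g or more: about +6 to -3 g.

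In one proportional run, control survivors averaged 2,006 g and saved infants 1,552 g. The gap of 454 g gave a shift of -20.0 g.

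**The case against.** The strongest reply is that this is detail for the statistical analysis plan. The article gives weight one line, defers model and missing-data detail to that plan, and words its secondary models for risks. The absence of a rule for infants who die is indeed not a defect of a condensed article, and a reader should not infer that the article prescribes a survivor-only analysis in so many words. What stands is narrower. The outcome as named is a mean weight, which a dead infant cannot have, and the clinical secondary measures are committed to unadjusted models plus models adjusted for covariates that differ across clusters. The deferral under the secondary analyses concerns missing data behind the primary results, and death before weighing is not ordinary missing data.

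It can also be said that birth weight might be one of the adjusting covariates. Nothing excludes it. But the Data analysis section selects covariates by baseline imbalance. Birth weight can be balanced at birth and still differ among survivors, so such a rule need not pick it up, and the unadjusted comparison is reported in any case.

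A reader might go further and infer that a successful trial would appear to impair growth. The documents do not support this. The outcome is weight, not gain, and the shift is near zero or slightly positive if the heavier infants are saved. A reader might also assume a gap as large as 1,000 g, which gives -44 g. The documents give no gap at all. If survivors average about 2,000 g at birth (assumed), it would put the typical saved infant near 1,000 g at birth, and the most extreme simulation reached only -32 g.

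Finally, mortality at 7 and 28 days is reported in the same infants, so a careful reader would see a survival difference beside any weight difference. That limits the harm but does not correct the comparison.

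**Conclusion.** The point holds in a limited form. Mean weight at 7 and 28 days is truncated by death in a trial that expects a mortality difference, and the stated adjustment does not address that. At the article's own mortality figures the artefact at day 28 is about -9 to -26 g for assumed gaps of 200 to 600 g, against a standard error of about 11 to 27 g. It can therefore be anything from negligible to large enough to reach significance. Sign and size depend on which infants are saved, and the documents do not settle this. The 4.4% share rests on the article's figures and on the assumption that the intervention causes no additional deaths; the gap, the SD and the ICC for weight are assumptions. The primary outcome, its power and the mortality-based safety outcomes are unaffected.

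**What to change.** State that the weight comparison at 7 and 28 days is among survivors. Make the main analysis either weight adjusted for each infant's own birth weight or gain from birth. Report it next to mortality at the same age, with the number weighed in each arm. An analysis that ranks deaths as worst may be added as a sensitivity analysis. It should not replace the main comparison, because it mixes weight with the mortality effect and could be positive through deaths alone.

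The cost is a change of wording. Birth weight is already recorded, is needed to enter this population, and is described in Outcome measures as unrelated to the intervention. Adjusting for it should also improve precision. The limitation is that adjustment removes only the part of the bias carried by birth weight: saved infants may differ from other survivors of the same birth weight, so the result still needs cautious reading.

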### Rationale for the trial

The effect of antenatal corticosteroids to reduce mortality and morbidity among preterm infants delivered in hospital settings in high-income countries is well-established
[4]. However, the impact of increasing antenatal steroid use in hospital or community settings without access to specialized services has not been well researched. Similarly, the safety of corticosteroids is well proven in women delivering at the hospital level; however, there is currently no clear evidence about the safety of antenatal corticosteroid use for community-level births.

This is a pragmatic cluster, randomized controlled trial designed to evaluate the effects of a multifaceted intervention that will improve the identification of pregnancies at high risk of preterm birth and will provide and facilitate the appropriate use of corticosteroids to women at risk of preterm delivery, with the goal of reducing neonatal mortality rates among preterm infants in communities with low antenatal corticosteroid use. The intervention will target the health system as whole, not individual patients.

Our hypothesis is that the multifaceted intervention will improve the identification and referral of pregnant women at high risk of preterm birth, increase the availability of antenatal corticosteroids and facilitate their appropriate use in eligible women and thus reduce neonatal mortality at 28 days in preterm newborns by 25%. We also hypothesize that the therapy will be safe for women and their newborns. Dexamethasone phosphate is the drug of choice for this study because it is readily available in the participating countries. This drug is used as the standard of care at the hospital level for women at risk of preterm birth at many of the sites. The primary objective will be to evaluate whether a cluster-level multifaceted intervention, including components to improve the identification of pregnancies at high risk of preterm birth and to provide and facilitate the appropriate use of corticosteroids, reduces neonatal mortality at 28 days of life in preterm newborns, compared with the standard delivery of care. The secondary objective is to determine whether the intervention is safe for women and their newborns.

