### The intervention

#### General outline

The study intervention will be (1) to provide antenatal corticosteroids kits (ready-to-use boxes containing corticosteroid vials, syringes, gloves, and instructions for administration) (2) to improve the identification and referral of women at high risk of preterm birth by training birth attendants to identify eligible women, (3) to post eligibility reminders at health facilities and in the boxes, (4) to measure uterine height with a color-coded tape to estimate GA in women with unknown GA, (5) to improve the administration of antenatal corticosteroids to eligible women by training birth attendants on its administration and encouraging its use through reminders at all primary health care levels and at all health care levels in which women at high risk of preterm birth could be attended.

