### Improving the identification of eligible women

Treatment (antenatal corticosteroid injection) and referral will be recommended for all pregnant women who are between 24 and 36 weeks GA and present with any of the following
[19]: *Signs of labor, or threatened labor* (intermittent abdominal pain, pain associated with blood-stained mucus discharge, watery vaginal discharge or a sudden gush of water, or any combination of these), *amniotic fluid leakage* (watery vaginal discharge or a sudden gush of water), *hemorrhage* (vaginal bleeding with or without cramping), *hypertension* (diastolic blood pressure of 90 mmHg or more on two consecutive readings taken at least 4 hours apart or 110 mmHg or more on one reading). In communities where blood pressure cannot be measured, women with eclampsia or signs or imminent eclampsia (e.g. severe headache) will be offered corticosteroids.

In some of the study communities, it is expected that an estimation of GA in women with signs of labor or pregnancy complications will not be available. Preliminary data from a previous GN study suggest that misclassification of preterm deliveries is significant
[20]. Additionally, data from the GN sites suggest that approximately 15% of women giving birth at the community level do not know the date of their LMP.

As part of the development of the intervention, we conducted a study to test a color-coded tape that we developed to identify preterm pregnancies between 24 and 36 weeks GA through fundal height measurement. Uterine fundal height measured by the color-coded tape will be used as a proxy for GA when reliable GA assessment is not available (Figure
4). The tape can be used in all pregnant women presenting with any of the risk factors and an unknown GA. The tape is divided in two segments, each shaded a different color; one segment clearly indicates the uterine height corresponding to the 24–36 weeks GA range. If LMP or estimated date of delivery is known, GA will be assessed using a specially designed obstetric disk (Figure
5). The use of the tape and obstetric disk will not be promoted for women with an ultrasound report verifying GA.

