### Intervention training

All the health providers potentially involved in delivery attendance at intervention clusters will be trained to deliver the intervention during an interactive *train-the-trainer workshop.* Workshop participants will learn how to (1) identify those women eligible for antenatal corticosteroids administration and (2) appropriately use the preterm kit, if legally allowed to administer injections, and (3) refer the woman to a health center or contact a skilled birth attendant when indicated. We will adapt the workshops’ format according to the targeted health providers.

All birth attendants working in the intervention clusters are eligible for participation in the trial if they provide care to pregnant women, assist in the delivery of babies, and assist the women in caring for their babies. We anticipate that approximately 3,000 birth attendants will be trained. All eligible birth attendants will be fully briefed on the study before training and will be asked to sign a Decline Form if they are not willing to receive the training.

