### Outcome measures

The primary outcome measure is neonatal mortality at 28 days of life in preterm infants in all clusters. LBW will be used as a proxy for preterm birth because in GN sites approximately 15% of the women who delivered at health centers or homes did not know their LMP dates, and 40% of the deliveries occurred at the community level, where ultrasound is not available. Thus, pragmatically, it is not possible to use gestational age to classify preterm births in these settings.

The variable to be used for classifying preterm births needs to be objective and unbiased in both intervention and control clusters. Thus it should be unrelated to the experimental intervention. The color-coded tape (Figure
4) is part of the intervention and will be used to improve the identification of pregnancies at high risk of preterm birth, but only in the intervention group. Therefore it is expected that this group will show more reliable gestational age assessment during the intervention period. Consequently, using gestational age to select the preterm group will likely introduce selection bias in the analysis.

Birth weight can be measured equally in both intervention and control clusters, and it is unrelated to the intervention. Birth weight measurement in the GN clusters is currently being done with high coverage (90%) and good quality. It is likely that some misclassification with small-for-gestational age (SGA) babies will exist, and that this misclassification can underestimate the real benefit of corticosteroids. But it is a conservative approach that will not introduce bias to the comparison between groups.

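### Mortality by setting is split on actual place of delivery, which the referral component is meant to change, so within-setting arm comparisons are open to selection bias of unknown size and direction

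*Protocol article*

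**What the plan says.** Among the secondary outcomes for infants below the site's 10th birth-weight percentile, Table 1 has the row "Neonatal and perinatal mortality rates by type of setting (health facility based deliveries vs. community based deliveries". Setting is thus defined by where the delivery took place. The article does not define it by a pre-intervention characteristic and does not call the row descriptive. In the section on other secondary outcome measures, intervention effects on the clinical measures are to be estimated with GEE and mixed models, unadjusted and adjusted.

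Referral runs through the description of the intervention:

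- Rationale for the trial: the hypothesis is that "the multifaceted intervention will improve the identification and referral of pregnant women at high risk of preterm birth".
- General outline: one component is "to improve the identification and referral of women at high risk of preterm birth by training birth attendants to identify eligible women".
- Section on identifying eligible women: the stated rule is "Treatment (antenatal corticosteroid injection) and referral will be recommended for all pregnant women who are between 24 and 36 weeks GA", given labour signs, fluid leakage, haemorrhage or hypertension.
- Intervention training: workshop participants learn to "refer the woman to a health center or contact a skilled birth attendant when indicated".

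On the variable that classifies preterm births, the Outcome measures section says: "Thus it should be unrelated to the experimental intervention". It rejects gestational age because the intervention would alter how it is assessed in one arm only.

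**The concern.** Women are referred because they show signs of risk, and the training to refer them is given in intervention clusters only. If referral changes where some of them deliver, community births in the intervention arm are those left after this group has moved, and facility births include the added group. A comparison of arms within either setting then mixes any real effect with a change in who is in the setting. Strictly, this is selection bias from conditioning on a variable that the intervention affects.

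The background and rationale stress how little is known about these drugs for births outside hospital. Readers will look to this row for an answer on community births, and it cannot give an unbiased one as defined.

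**Working it through.** **Plan's own figure.** The plan gives no figure for the setting-specific comparison. Its nearest figure is the power for the primary outcome: 90 clusters of 60 low-birth-weight births, 13% against 9%, slightly more than 80%. With 45 clusters per arm, a two-sided 0.05 test (assumed) and design effect 1 + 59 × ICC, an ICC of 0.03 gives 1 + 59 × 0.03 = 2.77. The effective size is 2,700 / 2.77 = 975 per arm and the power about 81%. The figure reproduces inside the stated ICC range of 0.01 to 0.05, so the 13% can be used as the base rate.

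**Inputs from the protocol.** The community share is taken from "40% of the deliveries occurred at the community level"; this refers to all deliveries and is assumed here for low-birth-weight births. Mortality of 13% comes from Power estimates.

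**Assumed inputs.** s is the share of all low-birth-weight births moved from community to facility in the intervention arm. x is the risk of the moved births relative to the average community risk. rc and rf are the control-arm community and facility risks. No infant's own risk changes.

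**Formulas.**

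- Intervention-arm community risk = (0.40·rc − s·x·rc) / (0.40 − s)
- Intervention-arm facility risk = (0.60·rf + s·x·rc) / (0.60 + s)

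**Results with rc = rf = 13% and x = 2.**

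| s | Community | RR | Facility | RR |
|---|---|---|---|---|
| 0.02 | (0.0520 − 0.0052)/0.38 = 12.3% | 0.95 | (0.0780 + 0.0052)/0.62 = 13.4% | 1.03 |
| 0.05 | (0.0520 − 0.0130)/0.35 = 11.1% | 0.86 | (0.0780 + 0.0130)/0.65 = 14.0% | 1.08 |
| 0.10 | (0.0520 − 0.0260)/0.30 = 8.7% | 0.67 | (0.0780 + 0.0260)/0.70 = 14.9% | 1.14 |

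Unsplit mortality stays at 13.0% in both arms in every row. In the last row, for example, 0.30 × 8.67% + 0.70 × 14.86% = 13.0%.

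**Chance of a false significant community result.** Take 45 clusters per arm, 24 community births per control cluster (60 × 0.40), 60 × (0.40 − s) per intervention cluster and an ICC of 0.02. For s = 0.10 the effective sizes are 1,080/1.46 = 740 and 810/1.34 = 604. A two-sided 0.05 test of 13.0% against 8.7% then rejects about 72% of the time. The same calculation gives about 19% for s = 0.05 and 7% for s = 0.02.

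**Cases with no bias or a different sign.**

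- x = 1 with equal setting risks: both risk ratios are 1.00.
- rc = 10%, rf = 15%, s = 0.10, x = 1.2: community (0.040 − 0.012)/0.30 = 9.3%, RR 0.93; facility (0.090 + 0.012)/0.70 = 14.6%, RR 0.97. Both settings look better.
- rc = rf = 13%, s = 0.10, x = 0.8 (the riskiest women cannot be moved in time): community (0.0520 − 0.0104)/0.30 = 13.9%, RR 1.07; facility (0.0780 + 0.0104)/0.70 = 12.6%, RR 0.97. The pattern is reversed.

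**Does anything planned remove the bias?** The Data analysis section adjusts for baseline imbalances, with the proportion of hospital births as an example. That does not correct a shift that arises after randomisation. Newborn-care training in both arms also mentions referral, but as part of caring for small infants, so it does not equalise antenatal referral. The number of referrals is a process measure, and process measures are taken in intervention clusters only, so it cannot show a difference between arms.

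**The case against.** The strongest reply is that the size rests wholly on assumptions. The protocol gives no expected shift, no mortality for referred women and no mortality by setting. A 10-point shift would mean that a quarter of community low-birth-weight births change place. The protocol also gives reasons to expect less: attendants may call a skilled provider instead of referring, kits are taken to home births, and the low-birth-weight group includes term small babies outside the 24 to 36 week range. All of this stands. A 2-point shift at twice the risk does little harm.

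A reader might infer that the row will favour the intervention in the community and make it look harmful in facilities. The documents do not support that. It requires the moved births to be riskier than both the community and the facility average, and the last two cases in the working give other patterns.

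It may also be said that a one-line table entry leaves its definition to an analysis plan not shown here. That holds for model details. The row itself, however, names the type of delivery as the split, and the text commits to estimating intervention effects on clinical measures.

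**Conclusion.** The point holds as a limited one about a single secondary outcome. Because setting is actual place of delivery and risk-selective referral is part of the intervention, within-setting arm comparisons are open to selection bias. This follows from the protocol alone and breaks the principle that it applies to gestational age.

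The size and sign do not follow from the protocol. The community risk ratios of 0.95 to 0.67 and facility risk ratios of 1.03 to 1.14 are illustrations under the stated assumptions. The upper end of the assumed shift gives a false 33% community reduction, larger than the 25% to 30% that the trial expects to find.

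A reader might also take this as a flaw in the trial's main result. It is not: the primary outcome, the all-infant mortality outcomes and the maternal infection outcomes are not split by place of delivery, and analysis follows the assigned cluster.

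**What to change.** 1. In Table 1 and the analysis plan, label mortality by actual place of delivery as descriptive, with no between-arm effect estimate or test within a setting.
2. Beside it, report the distribution of place of delivery by arm, so that any shift is visible.
3. For any claim of effect by setting, use the interaction between arm and each cluster's proportion of facility deliveries in the pre-randomisation registry data. Enter it as continuous or with a prespecified absolute cutoff, and adjust for site. A split at each site's median would serve poorly: where nearly all births share one setting, half the clusters would still be labelled as the other kind, and Argentina has only 6 clusters.

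The cost is wording. The registry baseline is already used for randomisation, and the Data analysis section already names the proportion of hospital births as a cluster-level variable. The downside is that the modifier describes clusters and not individual births. It is coarser and of limited power, and should be called exploratory.
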